#### 6.2.2 During Treatment

Regular visits will include registration of AE in the CRF and secure vaccinations and sampling of plasma and PBMC according to protocol for exploratory immune analysis at time-points as stated in section 6.1 (Table 2) and 7.1.2 (Table 3). Standard clinical follow-up (sputum cultures/AFS, clinical examination, routine blood samples, X-ray) will be performed at regular time-points. S-hCG will be analysed in females in the etoricoxib treatment study arms at every visit to check for pregnancy and in the H56:IC31 vaccine arms day 56 and 98 in addition to urine-HCG day 84 and day 140 immediately before immunisation.

Pharmacokinetic analysis (AUC, Cmax) with repetitive serum sampling will be performed during one day in the period between day 7-14 after initiation of etoricoxib when the patients still are in hospital (arm #1).

### **6.2.3 End of Treatment Visit**

All study arms will have an “End of Treatment visit” taking place at day 140 when etoricoxib treatment will be stopped and/or last (2nd) H56:IC31 immunisation is given.

All study arms will also have a control at day 154 and day 182 (or at later time-point according to clinical evaluation when anti-TB chemotherapy will be stopped).

### **6.2.4 Withdrawal Visit**

If the patient is withdrawn from the study before completing the study the patient will still be followed and receive standard anti-TB chemotherapy for 26 weeks or as long as needed as determined by the responsible clinician according to clinical guidelines.

### **6.2.5 After End of Treatment (Follow-up)**

All study arms will also have final follow-up controls and blood sampling for immune analysis and chemistry according to protocol (Table 2) at day 210 and 238 (10 and 14 weeks after etoricoxib treatment is stopped and last H56:IC31 immunisation is performed (resp. 4 and 8 weeks after anti-TB chemotherapy is ended).

## **6.3 Criteria for Patient Discontinuation**

### **6.3.1 Rules for Discontinuing the whole Study in an Individual Subject**

Patients may be discontinued from study treatment and assessments at any time. Patient is also at any time free to discontinue his/her participation in the study, without any further explanation or prejudice to further treatment.

Specific reasons for discontinuing a patient for this study are:

- Safety reason as judged by the Principal Investigator
- Major protocol deviation
- Incorrect enrolment ie, the patient does not meet the required inclusion/exclusion criteria for the study
- Patient's non-compliance to study treatment and/or procedures
- Patient lost to follow-up
- A female patient becoming pregnant
- TB disease progression
- Development of autoimmune disease or immunosuppression
- Death
- Other

### **6.3.2 Specific Rules for Discontinuing etoricoxib in an Individual Subject**

- An objective clinical or laboratory parameter change which meets Grade 3 or Grade 4 severity, as defined in the protocol toxicity table, AND is judged to be possibly, probably, or definitely related to etoricoxib.

- Deterioration in the patients condition which in the opinion of the Principal Investigator warrants study medication discontinuation (to be records as an AE or under Investigator Discretion).

### **6.3.3 Rules for Discontinuing Vaccine Injections in an Individual Subject**

Administration of additional study injections will be discontinued for an individual subject if he/she has any of the following:

- An objective clinical or laboratory parameter change which meets Grade 3 or Grade 4 severity, as defined in the protocol toxicity table, AND is judged to be possibly, probably, or definitely related to study vaccine.
- Fever (oral temperature  $\geq 39^{\circ}\text{C}$ ) within 1 week following study injection which is associated with constitutional symptoms (myalgia, arthralgia, fatigue, headache, anorexia, hives, chills) AND is judged to be possibly, probably, or definitely related to study injection.
- Injection site reaction that involves severe induration ( $>10$  cm, prevents daily activity or necrosis/ulceration), erythema ( $>10$  cm or necrosis/ulceration/ exfoliative dermatitis), tenderness (significant discomfort at rest or study site visit or hospitalization) or pain (any use of narcotic pain reliever or prevents daily activity or study site visit or hospitalization).
- Any event that in the opinion of the principal investigator precludes administration of any further study injections.

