### 5.4 Clinical Monitoring

Regular visits performed by the clinical investigators and study nurse will include registration of compliance, adverse events, routine clinical follow-up and examinations (*Mtb* cultures/microscopy/PCR/Gene Xpert, routine blood samples included biochemical parameters associated with organ toxicity, X-ray). S-hCG will be analysed in females to exclude pregnancy (section 6.2.2). Sampling of biobank for primary immunogenicity and exploratory studies according to time-points as stated in section 6.1 (table 1).

In addition, the study nurse will after individual evaluation keep in contact with the participants to secure compliance and safety issues. If there is any question of concern the participants will be seen at an extra visit within few days depending on the issue.

The study arms receiving H56:IC31 vaccine will be monitored for 60 minutes after administration of study vaccine to insure that no acute allergic events are in process and to see if a febrile response is developing. The participants will be examined frequently at time-points as stated in section 6.1 (table 2) to evaluate the physical manifestations of the immunization and with blood samples to assess the biochemical parameters associated with organ toxicity.

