## 17.5 Appendix 5 Supplementary Table 17- Toxicity Table

*Note: From final US FDA guidance: "Toxicity Grading Scale for Healthy Adult and Adolescent Subjects Enrolled in Preventive Vaccine Clinical Trials (September 2007) and for some values "Division of AIDS (DAIDS) Table for Grading the Severity of Adult and Pediatric Adverse Events Version 2.0" (November 2014). The laboratory values provided in the tables serve as guidelines and are dependent upon institutional normal parameters laboratory values.*

| Local Reaction to Injectable Product | Mild (Grade 1)                                  | Moderate (Grade 2)                                                                | Severe (Grade 3)                                             | Potentially Life Threatening (Grade 4)       |
|--------------------------------------|-------------------------------------------------|-----------------------------------------------------------------------------------|--------------------------------------------------------------|----------------------------------------------|
| Pain                                 | Does not interfere with activity                | Repeated use of non-narcotic pain reliever > 24 hours or interferes with activity | Any use of narcotic pain reliever or prevents daily activity | Emergency room (ER) visit or hospitalization |
| Tenderness                           | Mild discomfort to touch                        | Discomfort with movement                                                          | Significant discomfort at rest                               | ER visit or hospitalization                  |
| Erythema/Redness*                    | 2.5 – 5 cm                                      | 5.1 – 10 cm                                                                       | > 10 cm                                                      | Necrosis or exfoliative dermatitis           |
| Induration/Swelling**                | 2.5 – 5 cm and does not interfere with activity | 5.1 – 10 cm or interferes with activity                                           | > 10 cm or prevents daily activity                           | Necrosis                                     |

\* In addition to grading the measured local reaction at the greatest single diameter, the measurement should be recorded as a continuous variable.

\*\* Induration/Swelling should be evaluated and graded using the functional scale as well as the actual measurement.

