## Visit 7- (day 98)

1. Record any adverse events, including serious adverse events and adverse events of special interest occurring since previous evaluation; record any concomitant medications taken associated with treatment of the adverse event.
2. Focused physical examination by medical practitioner if indicated based on history
3. Vital signs: Blood pressure, pulse, temperature. Weight
4. **Blood collection/number of tubes:**
  - a. Serum chemistry/hematology: **1 EDTA tube (4 ml), 1 serum tube (5 ml).**
  - b. Blood hcg for all females of childbearing potential.
  - c. Biobank: **1 Natrium heparine tube\*(=WHOLE BLOOD), 4 CPT tubes, 1 Pax gene tube.**
5. Anti TB chemotherapy: standard combination therapy. Register any changes in medication in CRF
6. Drug dispensing and collecting: Collect and record any excessive study medication and empty medicine containers and if needed: hand out new study medication (Etoricoxib) for studyarms #1 and #4. Register in drug accountability log.
7. Examine site of vaccination, study arms #2 and #4

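### The vaccine-stopping rule in 6.3.3 counts a study site visit for injection-site pain or tenderness, where the toxicity table counts an ER visit, so a Grade 1 or 2 reaction that prompts a visit can end vaccination

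*Protocol*

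**What the plan says.** Section 6.3.3 opens with a mandatory instruction: "Administration of additional study injections will be discontinued for an individual subject if he/she has any of the following". Four bullets follow, and any one of them is enough.

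- The first bullet refers to the protocol's own grading: "An objective clinical or laboratory parameter change which meets Grade 3 or Grade 4 severity, as defined in the protocol toxicity table", together with a judgement that the change is related to the vaccine.
- The third bullet deals with local reactions. It begins "Injection site reaction that involves severe induration" and goes on to erythema, tenderness and pain. Its tenderness criterion is "tenderness (significant discomfort at rest or study site visit or hospitalization". Its pain criterion is "pain (any use of narcotic pain reliever or prevents daily activity or study site visit or hospitalization".

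The toxicity table (Appendix 5, repeated as Supplementary Table 2) grades the same two reactions. Its Grade 4 entry for pain is "Emergency room (ER) visit or hospitalization", and the tenderness row has the same entry with ER abbreviated.

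Section 5.4 sets a low threshold for bringing participants in: "If there is any question of concern the participants will be seen at an extra visit within few days depending on the issue".

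**The concern.** An individual stopping rule should give the same answer for the same reaction. Here two bullets of one section can disagree. The first follows the toxicity table, while the third uses a term that is not in the table's pain or tenderness rows and that 6.3.3 does not define. A visit to the study site is something the trial staff can arrange, and section 5.4 tells them to do so readily. It does not measure how severe the reaction is.

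What is at stake is the second injection. With 10 patients planned per arm, one second dose withheld is 1/10 = 10% of a vaccine arm. Section 10.4.6 keeps anyone with at least one vaccine dose in the immunogenicity analysis, so that patient would not drop out of it. One-dose and two-dose patients would instead be mixed in the day 84 to day 154 comparison.

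**Working it through.** The plan states no figure that could be reproduced here. The check sets the texts side by side, applies the rule to a case, and then looks at the reported dosing.

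**1. Wording compared (paraphrased)**

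| Reaction | Table, Grades 1–2 | Table, Grade 3 | Table, Grade 4 | 6.3.3, third bullet |
|---|---|---|---|---|
| Pain | from no effect on activity up to interference, or repeated non-narcotic analgesia | narcotic analgesia, or daily activity prevented | ER visit or hospitalization | the Grade 3 text, or **study site visit**, or hospitalization |
| Tenderness | discomfort to touch, or on movement | marked discomfort at rest | ER visit or hospitalization | the Grade 3 text, or **study site visit**, or hospitalization |

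For both reactions the third bullet reproduces Grades 3 and 4 with one term replaced.

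**2. The rule applied to one reaction under two follow-up practices**

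Take a vaccinee with Grade 1 injection-site pain after the first dose.

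- Staff deal with it by telephone. First bullet: not Grade 3 or 4, so not met. Third bullet: no narcotic use, activity not prevented, no visit, so not met. The second dose goes ahead.
- Staff call the patient in under section 5.4. First bullet: still not met. Third bullet: pain with a study site visit, so met as worded. Further injections must stop.

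The grade is the same in both cases, but the outcome differs. The fourth bullet, on the principal investigator's opinion, adds a ground for stopping and gives no power to set the third bullet aside.

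**3. What the reported data show**

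- Combination arm (etoricoxib plus H56:IC31): 8 patients received the first dose and 8 the second, so 8 − 8 = 0 lost. Vaccination-site pain is listed for 2 patients in the day 0–84 table.
- H56:IC31 arm: 11 received the first dose and 10 the second, a net difference of 11 − 10 = 1. The events listed as leading to discontinuation in the day 85–154 table are lymphadenopathy and abdominal pain.
- No injection-site reaction appears in the severe-event or discontinuation tables for either interval.

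The tables do not say whether any patient's site pain prompted a visit, or was still present at one.

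**The case against.** The strongest reply has four parts.

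*The third bullet may be a deliberate rule of its own.* It does not cite the toxicity table, and the first bullet is confined to objective changes, which pain and tenderness arguably are not. Section 8.8 places emergency care during immunization at the study's outpatient clinic, so a study site visit could be a local substitute for an ER visit. This is plausible, but the protocol does not say so, and it would still leave a precautionary visit indistinguishable from an emergency one.

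*The words mean a visit made because of the reaction.* This is the natural reading, and it stands. A reader might go further and infer that routine attendance alone costs a patient the second dose, pointing to the day 98 instruction: "Examine site of vaccination, study arms #2 and #4". The documents do not support that. The term sits inside a description of an injection-site reaction, so attendance without pain or tenderness triggers nothing. Counting a compulsory visit would also make the criterion true for every attending patient with any soreness, in a list that begins with severe induration. The natural reading does not remove the problem, however, because an extra visit under section 5.4 for mild pain is a visit made because of the reaction.

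*The bullet lacks a relatedness condition.* A reader might see this as a second defect, since the first two bullets have one. It is not: an injection-site reaction is already tied to the injection.

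*No effect is visible, and none can be predicted.* Section 8.2 gives a frequency of at least 10% for a pooled list of vaccine reactions and none for visits prompted by pain, so any forecast of lost doses would rest on an assumed rate. The reported dosing shows no loss. Both points stand and limit the finding to the wording.

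**Conclusion.** The inconsistency holds. Section 6.3.3 and the toxicity table set different criteria for the same two local reactions, and the term that differs is undefined. On the natural reading, a Grade 1 or 2 reaction that leads to a precautionary visit meets a mandatory stop without reaching Grade 3 or 4. This conclusion assumes only that an extra visit under section 5.4 counts as a study site visit, and nothing in the text excludes that.

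The size is small: one term in two criteria, with no second dose reported lost to an injection-site reaction. The absence of losses fits with sites not having applied the wording literally, but it does not establish which reading they used. Which threshold is clinically right is not judged here.

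**What to change.** Reconcile the pain and tenderness wording in the third bullet of 6.3.3 with the corresponding rows of the toxicity table, and state which kind of visit, if any, counts towards stopping. The sponsor and investigator decide which wording stands.

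The cost is a few words in an amendment, handled under section 11.4, with no added data or staff. Because results are already reported, one sentence in the study report saying which reading was applied would serve the same purpose for readers.

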## **6.4 Procedures for Discontinuation**

### **6.4.1 Patient Discontinuation**

Patients who withdraw or are withdrawn from the study, will stop further etoricoxib treatment and/or and not receive vaccine immunization. The patient will still be followed and receive standard anti-TB chemotherapy for 26 weeks or as long as needed as determined by the responsible clinician according to clinical guidelines.

If the 1st H56:IC31 injection is missed (day 84) due to other reasons than in 6.3.3, the 2nd injection (day 140) can still be given and the patient continue to be included in the study.

The reason for discontinuation will be recorded. Any significant AE will be followed-up until the outcome either is recovered or resolved.

Patients who withdraw or are withdrawn from the study within the first 98 days of the study will be replaced.

### **6.4.2 Trial Discontinuation**

The whole trial may be discontinued at the discretion of the PI or the sponsor in the event of any of the following:

- Occurrence of AEs unknown to date in respect of their nature, severity and duration
- Medical or ethical reasons affecting the continued performance of the trial
- Difficulties in the recruitment of patients
- Cancellation of drug development

The sponsor and principal investigator will inform all investigators, the relevant Competent Authorities and Ethics Committees of the termination of the trial along with the reasons for such action. If the study is terminated early on grounds of safety, the Competent Authorities and Ethics Committees will be informed within 15 days.

## **6.5 Laboratory Tests**

Blood samples will be drawn by venepuncture. Plasma, serum and PBMCs will be isolated, frozen and stored in the Department of Infectious Diseases, Oslo University Hospitals approved "Research Biobank Infectious Diseases." Principles governing biomedical research in humans as stated in the Declaration of Helsinki will be followed. See Section 7 regarding the analysis to be performed

Routine sputum, tissue and blood samples as part of the clinical diagnosis and follow-up of TB will be collected, handled and analysed in accordance with hospital/laboratory standard procedures.

## **7 ASSESSMENTS**

### **7.1 Immunogenicity and Immunology Analyses**

A summary of immunologic assays to be performed on blood specimens is shown in Table 3. Listed blood volumes are estimates. Blood will be collected for all assays. Required assays will be performed on available specimens from all listed subjects and time points. Exploratory assays may be performed on specimens from certain subjects and time points.

#### **7.1.1 Immunogenicity and Immune variables**

##### **7.1.1.1 Flow cytometry**

Immune responses to *in vitro* stimulation of whole blood or PBMC with H56 antigenic peptide pools (Ag85B, ESAT-6, and Rv2660c) and with peptides representing non-vaccine Mtb-derived antigens (CFP10, TB10.4, PPD) will be analysed in all study arms and assessed by:

- Cytokine producing CD4+ and CD8+ T cells (intracellular cytokine staining; ICS).
- T cell proliferation (cfse)
- Tregulatory cells (CD45RA, CD25, FoxP3, PD1)
- Monocyte, T cell and Treg COX-2i expression
- Soluble cytokines and PGE2 levels in plasma and cell supernatants analyzed by multiplex and ELISA

##### **7.1.1.2 ELISPOT**

Immune responses to *in vitro* stimulation of whole blood or PBMC with H56 antigenic peptide pools (Ag85B, ESAT-6, and Rv2660c) and CFP10: IFN- $\gamma$ /IL-2 spot-forming units (SFU) /10^6 PBMC pre- and post-vaccination and the effect of COX-2i will be determined.

##### **7.1.1.3 Transcriptional (RNA) biomarker analysis**

The relative upregulation of an expanded panel of genes of interest will be determined using dual-color Reverse-Transcriptase Multiple Ligation-dependent Probe-Amplification (dcRT-MLPA). In brief, total RNA is extracted from PAXgene blood collection tubes using the PAXgene Blood RNA kit (PreAnalytiX, DE) and relative expression is determined with dcRT-MLPA assay and analyzed on a 3730 capillary sequencer (Life Technologies, US).

#### 7.1.1.4 Mycobacterial growth inhibition assays (MGIA):

Vaccine immunogenicity will be assessed using MGIA, an *in vitro* challenge model assesses the ability of immune cells to control growth of *Mtb* in a controlled system. PBMCs will be infected with log phase *Mtb* and subsequently, the degree of mycobacterial growth (BACTEC MGIT 960), pre- and post-vaccination and the effect of COX-2i will be determined. This assay will be performed in BSL3 facilities at OUS or with collaborating partners.

#### 7.1.1.5 IgG and humoral immunity.

Antigen-specific IgG response to H56:IC31 will be determined in plasma samples by ELISA pre- and post-vaccination. This assay will be done at SSI in Denmark.

**7.1.2 Supplementary Table 16: Summary of Immunology Specimens and Assays**

| Assay                                                | Priority    | Purpose of assay                                                                                           | Location         | Study Days                                     | Volume per time |
|------------------------------------------------------|-------------|------------------------------------------------------------------------------------------------------------|------------------|------------------------------------------------|-----------------|
| ICS; whole blood/PBMC, (flow cytometry)              | Required    | Determine cellular immune response to study vaccine and TB                                                 | OUS, Norway      | 0, 84, 98, 140, 154, 238                       | 5 mL            |
| T cell proliferation PBMC, (flow cytometry)          | Required    | Determine cellular immunogenicity to study vaccine and TB                                                  | OUS, Norway      | 0, 84, 98, 140, 154, 238                       | 5 mL            |
| IFN- $\gamma$ /IL-2 PBMC (ELISPOT)                   | Required    | Determine cellular immunogenicity to study vaccine and TB                                                  | OUS, Norway      | 0, 84, 98, 140, 154, 238                       | 5 mL            |
| Vaccine IgG (ELISA)                                  | Exploratory | Determine humoral immunogenicity to study vaccine                                                          | SSI, Denmark     | 0, 84, 98, 140, 154, 238                       | 4 ml (plasma)   |
| MGIA                                                 | Exploratory | Determine in a in vitro challenge model the ability of immune cells to control growth of Mtb | To be determined | 0, 84, 98, 140, 154, 238                       | 10ml            |
| PaxGene for RNA analysis (transcriptional profiling) | Exploratory | Identify early gene signatures that can predict immune responses                                           | To be determined | 0, 84, 98, 140, 154                            | 3 mL            |
| PBMC (flow cytometry)                                | Exploratory | T cell and monocyte regulation, activation cytokine production and cox-2 expression                        | OUS, Norway      | 0, 14, 28, 56, 84, 98, 140, 154, 182, 210, 238 | 10 mL           |

